# A phase II study of carboplatin and etoposide plus durvalumab for previously untreated extensive-stage small-cell lung cancer (ES-SCLC) patients with a poor performance status (PS): NEJ045A study protocol

**DOI:** 10.1186/s12885-022-10222-1

**Published:** 2022-11-04

**Keywords:** Small-cell lung cancer, Poor performance status, Immune checkpoint inhibitor, Anti-PD-L1, Durvalumab

## Abstract

**Background:**

Small-cell lung cancer (SCLC) accounts for 12–15% of lung cancers and has a limited prognosis, with approximately one-third of SCLC patients having a poor performance status (PS). Patients with extensive-stage (ES) SCLC and a poor PS have a poor prognosis. For this population, overall survival from carboplatin and etoposide treatment is 7–8 months, and treatment development is an unmet medical need. Recently, the combination of an anti-PD-L1 (a ligand for programmed cell death 1) antibody and platinum-based chemotherapy has become the standard of care for ES-SCLC patients with a good PS (PS 0–1). We hypothesized that the combination of the anti-PD-L1 antibody durvalumab with carboplatin and etoposide would be feasible and effective for such patients.

**Methods:**

We initiated a multicenter phase II study of durvalumab combined with carboplatin and etoposide in previously untreated ES-SCLC patients with a poor PS (PS 2–3). Eligible patients will receive durvalumab plus carboplatin and etoposide every 3 to 4 weeks for up to 4 cycles, followed by durvalumab every 4 weeks until progression or unacceptable toxicity. The dosages of carboplatin and etoposide for the second and subsequent cycles will be adaptively determined based on the adverse events of the first cycle. A total of 56 patients (43 patients with a PS of 2 and 13 patients with a PS of 3) will be enrolled in this study, with a 24-month enrollment period and a 12-month follow-up. The primary endpoint is the tolerability of carboplatin and etoposide plus durvalumab in previously untreated ES-SCLC patients with a poor PS. The secondary endpoints are the 1-year survival rate, objective response rate, progression-free survival, overall survival, ratio of PS improvement, and safety.

**Discussion:**

The results of this study are intended to establish the safety and efficacy of carboplatin and etoposide plus durvalumab in patients with ES-SCLC and a poor PS.

**Trial registration:**

Japan Registry of Clinical Trials (jRCT), jRCTs031200319. Registered 21 January 2021, https://jrct.niph.go.jp/en-latest-detail/jRCTs031200319

## Background

Lung cancer is the leading cause of cancer-related deaths worldwide [1]. Small-cell lung cancer (SCLC) accounts for 12–15% of lung cancers. The age-adjusted incidence rate of SCLC in the U.S. was reported to be approximately 6 per 100,000 in 2016 according to an analysis of the SEER database [2]. SCLC has a limited prognosis (lung cancer-specific 2-year survival rates are only 11% for men and 17% for women), and the treatment of SCLC remains an important clinical challenge [2].

The standard of care for the first-line treatment of extensive-stage (ES) SCLC was platinum-based (platinum-doublet) chemotherapy (cisplatin or carboplatin and etoposide or irinotecan) for many years until the advent of combination therapy with immune checkpoint inhibitors (ICIs). Despite the high objective response rate (ORR) of cisplatin and irinotecan or cisplatin and etoposide (60–80%), the overall survival (OS) duration is approximately only 10–13 months for patients with a good Eastern Cooperative Oncology Group (ECOG) performance status (PS) [3–6].

Because of the rapid progression of SCLC, many patients are in a poor general condition at the time of diagnosis. A previous study reported that 51 (35%) of 145 patients with SCLC had a PS of 2–3 [7]. For patients with a poor PS (PS 2–3), carboplatin and etoposide have been one of the standard-of-care treatments for untreated ES-SCLC based on the Japan Clinical Oncology Group (JCOG) 9702 study [8]. This randomized phase 3 trial compared carboplatin (area under the curve [AUC] 5, day 1) and etoposide (80 mg/m^2^, days 1–3) with cisplatin and etoposide in divided doses (split PE) in patients with a PS of 3 and aged less than 70 years or those with a PS of 0 to 2 and aged 70 years or older. The median progression-free survival (PFS), median OS, and 1-year survival rates of carboplatin and etoposide vs. split PE were 5.2 vs. 4.7 months, 10.6 vs. 9.9 months, and 41% vs. 35%, respectively. In the subgroup analysis, the median OS for patients with a PS of 2–3 treated with carboplatin plus etoposide vs. split PE was 8.3 months vs. 8.1 months. Although grade 3 or 4 hematologic toxicities, such as leukopenia (grade 3 or higher: 54%), neutropenia (95%), anemia (29%), and thrombocytopenia (56%), were observed among all patients treated with carboplatin and etoposide, most toxicities were tolerable, and treatment compliance was favorable. Although adverse events in patients with a poor PS were not reported in this study, 74% of patients had a PS of 0–1 and were aged 70 years or older in the JCOG 9702 study, and patients with a poor PS had more frequent adverse events than those with a good PS.

Recently, the combination of an ICI and platinum-based chemotherapy has become a standard of care for chemotherapy-naïve ES-SCLC patients with a PS of 0–1. Programmed cell death-1 (PD-1) and PD-1 ligand-1 (PD-L1) play an important role in tumor immune evasion. The addition of an anti-PD-L1 antibody to conventional chemotherapy enhances tumor-specific T cell immunity by inhibiting the PD-1/PD-L1 pathway [9]. In a phase III trial (CASPIAN) that compared durvalumab (1500 mg) plus platinum-based chemotherapy with conventional platinum-based chemotherapy (cisplatin 75–80 mg/m^2^ and etoposide 80–100 mg/m^2^ or carboplatin AUC 5–6 and etoposide 80–100 mg/m^2^) in previously untreated ES-SCLC patients, platinum-based chemotherapy and durvalumab significantly prolonged OS, which was the primary endpoint (median OS 13.0 months in the study group vs. 10.3 months in the control group; hazard ratio (HR) 0.73 [95% confidence interval (CI) 0.59–0.91]; *p* = 0.0047) [10]. The response rate was significantly higher in the study treatment group (68%) than in the standard treatment group (58%) (odds ratio 1.56 [95% CI 1.10–2.22]). In a phase III study (IMpower133) on the addition of atezolizumab (1200 mg), an anti-PD-L1 antibody, to conventional platinum-based chemotherapy (carboplatin AUC 5 and etoposide 100 mg/m^2^), carboplatin and etoposide with atezolizumab prolonged OS compared with carboplatin plus etoposide (12.3 months in the study group vs. 10.3 months in the control group; HR 0.70 [95% CI 0.54–0.91]; *p* = 0.007) [11].

The combination of immune checkpoint inhibitors with cytotoxic chemotherapy has a synergistic effect and improves efficacy in ES-SCLC patients with a good PS. However, despite the high frequency of ES-SCLC patients with a poor PS, there remains an unmet need to explore the combination therapy of an ICI and platinum-doublet chemotherapy in these patients. Since SCLC is highly sensitive to cytotoxic chemotherapy, we hypothesized that patients with ES-SCLC and a poor PS may benefit from anti-PD-L1 antibody therapy because tumor shrinkage by anticancer agents is expected to improve PS and tumor immune responses. Therefore, we planned a phase II study to evaluate the safety and efficacy of carboplatin and etoposide plus durvalumab for patients with chemotherapy-naïve ES-SCLC and a poor PS (PS 2–3).

## Methods

### Study design and objectives

NEJ045A is a phase II, nonrandomized, open-label, single-arm trial (Japan Registry of Clinical Trials protocol identification no. jRCTs031200319). The study scheme is shown in Fig. 1. The primary endpoint is the tolerability of carboplatin and etoposide plus durvalumab in previously untreated ES-SCLC patients with a poor PS (PS 2–3). The secondary endpoints are the 1-year survival rate, ORR, PFS, OS, ratio of PS improvement, and safety. Patients will receive carboplatin and etoposide plus 1500 mg durvalumab (day 1) every 3 to 4 weeks in the induction phase, followed by 1500 mg durvalumab every 4 weeks in the maintenance phase until progression or unacceptable toxicity. The initial doses of carboplatin and etoposide will be modified according to PS. In patients with a PS of 2, at the first cycle, patients will receive carboplatin AUC 4 (day 1) and etoposide 80 mg/m^2^ (days 1–3). If prolonged neutropenia (grade 4 or higher for 4 days or more), febrile neutropenia, grade 4 or higher thrombocytopenia, or grade 3 or higher nonhematologic toxicity is observed in the previous cycle, the doses of both drugs will be decreased by 75% those of the previous cycle: namely, carboplatin AUC 3 and etoposide 60 mg/m^2^. If the above adverse events are not observed in the previous cycle, the dose of either carboplatin or etoposide can be increased (carboplatin AUC 5 and/or etoposide 100 mg/m^2^), or the same dose can be continued. The dose of durvalumab will be fixed at 1500 mg. To ensure safety, six patients with a PS of 2 will be enrolled in the first study and then evaluated by the efficacy and safety evaluation committee. In patients with a PS of 3, at the first cycle, patients will receive carboplatin AUC 4 (day 1) and etoposide 80 mg/m^2^ (days 1–3). If the above adverse events are not observed in the previous cycle, the dose of either carboplatin or etoposide can be increased, or the same dose can be continued. The use of the granulocyte colony-stimulating factor is allowed as the primary and secondary prophylaxis of febrile neutropenia.

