### Statistical analysis

The primary endpoint, the tolerability of carboplatin and etoposide plus durvalumab in untreated ES-SCLC patients with a poor PS, will be evaluated based on the percentage of patients who complete four cycles of carboplatin and etoposide plus durvalumab. In the JCOG 9702 study, which evaluated carboplatin and etoposide in ES-SCLC patients with a PS of 3 and aged less than 70 years or with a PS of 0–2 and aged 70 years or more, demonstrated that 63% of patients completed 4 cycles [8]. Our study will include only patients with a poor PS; therefore, if 50% of patients complete 4 cycles, the study treatment will be considered tolerable. If the expected percentage of completion in patients with a PS of 2 is 50%, the threshold percentage of completion is 33%, the one-sided alpha error is 0.1, and the beta error is 0.2, the required number of patients is calculated to be 41 based on the exact binomial distribution. If the expected percentage of completion in patients with a PS of 3 is 50%, the threshold percentage of completion is 20%, the one-sided alpha error is 0.1, and the beta error is 0.2, the required number of patients is calculated to be 12 based on the exact binomial distribution.

The total number of patients was calculated to be 56, considering the patients excluded from the analysis due to censoring. For the 1-year survival rate, which is the most important secondary endpoint, under the expected value of 26%, a threshold of 13%, and alpha error of 0.1 (one-sided), the power of the exact test for the binomial ratio is calculated to be 85 and 78% under all 53 patients (sum of those with a PS of 2 and 3) and 41 patients with a PS of 2, respectively.

This study was approved by the Niigata University Central Review Board of Clinical Research. All procedures will be performed in accordance with the ethical standards of the institutional and/or national research committee and with the 2013 Declaration of Helsinki and its later amendments or comparable ethical standards. All patients must provide written informed consent.

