## Discussion

The safety and efficacy of adding ICIs to platinum-doublet chemotherapy for ES-SCLC patients with a poor PS are unclear, and this is the significance of this study. A systematic review demonstrated that non-small cell lung cancer patients with a poor PS had a worse prognosis than those with a good PS [12]. Furthermore, a heavy tumor burden was associated with poor responsiveness to ICIs [13] Because platinum-doublet chemotherapy has a high response rate in ES-SCLC patients, a decrease in the tumor volume by cytotoxic chemotherapy results in improved PS, antitumor immunity and responsiveness to ICIs. To ensure safety, the initial chemotherapy dose will be started at a reduced level, but the design allows for dose escalation from the second cycle onward so that the effect on efficacy is minimized.

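### Read literally, the Methods dose rule lets a PS 2 patient reduced after a toxicity be raised 25% above the dose that caused it, and the abstract names a different governing cycle

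*Protocol article*

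**What the plan says.** The operative rule is in the protocol article, Methods, Study design and objectives. PS 2 patients start at carboplatin AUC 4 and etoposide 80 mg/m². Four kinds of event trigger a reduction: grade 4 neutropenia lasting at least four days, febrile neutropenia, thrombocytopenia of grade 4 or worse, and nonhematologic toxicity of grade 3 or worse. After any of these, "the doses of both drugs will be decreased by 75% those of the previous cycle: namely, carboplatin AUC 3 and etoposide 60 mg/m^2". The raise is permitted where the same events are "not observed in the previous cycle, the dose of either carboplatin or etoposide can be increased (carboplatin AUC 5 and/or etoposide 100 mg/m^2"; continuing at the same dose is the stated alternative. PS 3 patients start at the same dose and may also be raised after a clean cycle, but no raised level is named for them.

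Two other places describe the same mechanism. The abstract (Methods) says that the chemotherapy doses "for the second and subsequent cycles will be adaptively determined based on the adverse events of the first cycle". The Discussion says that "the design allows for dose escalation from the second cycle onward".

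**The concern.** A rule that looks back one cycle forgets why a patient was reduced. Once a reduced patient has one clean cycle, the only stated condition for a raise is met, and the only raised level named lies above the dose at which the event occurred. Nothing in the section limits the raise to patients who were never reduced, or caps it at the earlier dose. The abstract points to a different cycle, so a reader cannot settle from the article which events govern cycles 3 and 4.

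What is at stake is possible re-exposure above a dose that has already produced a severe event, in a population about which the Background remarks that "patients with a poor PS had more frequent adverse events than those with a good PS". G-CSF "is allowed as the primary and secondary prophylaxis of febrile neutropenia". That stated use addresses one of the four triggers; it is not directed at thrombocytopenia or nonhematologic toxicity. Treatment tolerability is "evaluated based on the percentage of patients who complete four cycles of carboplatin and etoposide plus durvalumab", so the doses in cycles 3 and 4 are part of the regimen being judged, and a rule that 31 hospitals could read differently makes that regimen less well defined.

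**Working it through.** **Inputs** (Study design and objectives unless noted): start 4/80 (carboplatin AUC / etoposide mg/m²); reduction to 75% of the previous cycle, named as 3/60; raised level AUC 5 and/or 100 mg/m²; up to four induction cycles (abstract, Methods).

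**1. Reproduce the stated reduction.** 0.75 × 4 = 3 and 0.75 × 80 = 60. This matches the named level.

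**2. Check which starting levels the named reduction fits.**
- From 5/100: 0.75 × 5 = 3.75 and 0.75 × 100 = 75. No match.
- From 3/60: 0.75 × 3 = 2.25 and 0.75 × 60 = 45. No match.

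The named levels therefore describe one step down from 4/80.

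**3. Follow a PS 2 patient with an event in cycle 1 and a clean cycle 2.**

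| Cycle | Previous cycle | Dose under Methods, read literally |
|---|---|---|
| 1 | none | 4/80 |
| 2 | listed event at 4/80 | 3/60 |
| 3 | clean at 3/60 | up to 5/100, or stay at 3/60 |

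Size of the permitted raise, for each drug raised:
- against the reduced dose: 5/3 = 100/60 = 1.67, or +67%;
- against the dose that caused the event: 5/4 = 100/80 = 1.25, or +25%.

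Whether one drug or both may be raised is itself unclear, because the sentence uses an either/or form and then and/or in the bracket. The percentages apply to whichever drug is raised.

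**4. Apply the abstract's basis to the same patient.** Cycle 1 contained a listed event. If cycle 1 governs, that fact does not change, and the condition for a raise is not met in cycle 3 or cycle 4. Under Methods it is met in cycle 3. For cycle 2 the two agree, because the previous cycle is the first cycle; they part at cycles 3 and 4. The Discussion sentence does not decide between them.

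**5. Context for the raised level.** The Background gives the reference regimen for poor PS as "carboplatin (area under the curve [AUC] 5, day 1) and etoposide (80 mg/m^2^, days 1–3" mg/m² per the cited phase 3 trial's schedule. Against it, 5/100 is equal for carboplatin (5/5 = 1.00) and 25% higher for etoposide (100/80 = 1.25). The article reports grade 3 or 4 thrombocytopenia in 56% at that regimen, but the trigger here is grade 4 and 74% of that trial's patients were PS 0–1 and aged 70 or older. The figure cannot be turned into a number of patients affected.

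**6. Design figures.** The stated sample sizes and powers reproduce. For PS 2, n = 41 with at least 18 completers gives one-sided alpha 0.0955 and power 0.826. For PS 3, n = 12 with at least 5 completers gives 0.0726 and 0.806. None of these takes a dose as an input, so none changes.

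**The case against.** The strongest reply is that the rule was written for one decision only, the change from cycle 1 to cycle 2. Both named levels are one step from 4/80, and no increment is given for a patient already at 3/60. On that reading the previous cycle is the first cycle, the abstract agrees with Methods, and the Discussion merely names the earliest point for a raise. This is plausible and stands as a likely account of intent. It does not rescue the text: Methods does not say first cycle, and the abstract says that its basis covers subsequent cycles as well as the second. If only one step was meant, Methods states no rule for cycles 3 and 4.

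A second reply is that this is a condensed article. The full protocol may bar re-escalation, and the study scheme in Fig. 1 is not shown. That also stands, and the lack of a detailed dose-modification section is not the point here. The point is that the rule the article does state gives this result, and that two parts of the article name different cycles.

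Third, the raise is optional, and an efficacy and safety committee reviews the first six PS 2 patients. Both are true and lower the risk, although the committee review as described sets no limit on an individual patient's later dose.

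A reader might also infer that under the abstract's wording a toxicity after cycle 1 would trigger no reduction. The abstract is a one-line summary and does not say that; it only names a different governing cycle.

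**Conclusion.** The point holds as a loosely fixed and internally inconsistent dose rule. Read literally, Methods permits a PS 2 patient reduced to 3/60 after an event at 4/80 to be raised, after one clean cycle, to a level 25% above the dose that caused the event. The abstract's basis would not permit it. This rests on reading the previous-cycle condition as applying to every cycle, and the named raised level as applying to patients already reduced; the text allows both without stating either.

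A reader might go further and infer that patients will be re-escalated in this way, or that the completion rate will be distorted. The documents do not support either. The raise is at the investigator's discretion, the article gives no rate for the listed events at 4/80, and no effect on the primary endpoint is shown. The finding is a cheap safety clarification and has no bearing on the sample size or power.

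**What to change.** Add one sentence to the dosing rule in Study design and objectives: *A patient whose dose was reduced for a listed event will not be raised above the dose at which that event occurred.* Whether such a patient may return to that dose, for example to 4/80 with G-CSF cover after febrile neutropenia, is a clinical choice for the sponsor to state.

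In the abstract, replace *the first cycle* with *the previous cycle*, so that it names the same governing cycle as Methods.

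The cost is one sentence and one word, and slightly fewer escalations among patients who were reduced and then did well. If the full protocol already contains such a cap, only the published wording needs to be brought into line.

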**Fig. 1 Fig1:**
[figure not shown]
NEJ045A Study Design. Abbreviations: ES-SCLC, extensive-stage small-cell lung cancer; ECOG, Eastern Cooperative Oncology Group; PS, performance status; AUC, area under the curve; PD, progressive disease

### Key eligibility criteria

Key inclusion and exclusion criteria are shown in Table 1.

**Table 1 Tab1:** Key patient eligibility criteria

Inclusion Criteria	
• Histologically or cytologically confirmed SCLC • ES-SCLC that is not amenable to surgery or curative irradiation • No prior chemotherapy for SCLC • ECOG PS of 2 or 3 • Age 20 years or older at the time of consent • Patients with measurable lesions that are target lesions according to the RECIST version 1.1 • Adequate organ function • Neutrophil count: 1500/mm^3^ or more • Hemoglobin: 9.0 g/dL or more • Platelet count: 10.0 × 10^4^/mm^3^ or more • AST: 2.5 times or less the upper limit of the institutional standard (5 times or less the upper limit of the institutional standard in the case of liver metastasis) • ALT: 2.5 times or less the upper limit of the institutional reference value (5 times or less the upper limit of the institutional reference value if liver metastases are present) • Total bilirubin: 1.5 times or less the upper limit of the institutional standard (3 times or less in the case of indirect hyperbilirubinemia such as Gilbert’s syndrome) • SpO_2_ 93% or higher (or PaO_2_ 70 Torr or higher) • Serum creatinine: less than 1.5 mg/dL (or creatinine clearance 45 mL/min or more) • Written informed consent	
Exclusion Criteria	
• Patients with a usual interstitial pneumonia (UIP) pattern or probable UIP pattern on chest CT • Patients with meningeal carcinomatosis • Patients with a history of radiation to the primary lesion • Patients with pleural effusion, pericardial effusion, or ascites requiring drainage • Patients with coexisting autoimmune diseases (myasthenia gravis, myositis, autoimmune hepatitis, systemic lupus erythematosus, rheumatoid arthritis, inflammatory bowel disease, vasculitis, Sjogren’s syndrome, multiple sclerosis, etc.) • Patients with serious complications (active infection, symptomatic congestive heart failure, uncontrolled hypertension, unstable angina pectoris, fatal arrhythmia, respiratory, hepatic or renal disease, etc.) • Patients with concurrent multiple cancers or heterogeneous multiple cancers with a disease-free interval of 5 years or less • Other patients who are judged by the principal investigator or subinvestigator to be inappropriate for participation in this study	

*Abbreviations*: *ES-SCLC* Extensive-stage small-cell lung cancer, *ECOG* Eastern Cooperative Oncology Group, *PS* Performance status, *RECIST* Response Evaluation Criteria in Solid Tumors, *AST* Aspartate aminotransferase, *ALT* Alanine aminotransferase, *SpO*_*2*_ Percutaneous oxygen saturation, *PaO*_*2*_ Partial pressure of arterial oxygen, *CT* Computed tomography

### Statistical analysis

The primary endpoint, the tolerability of carboplatin and etoposide plus durvalumab in untreated ES-SCLC patients with a poor PS, will be evaluated based on the percentage of patients who complete four cycles of carboplatin and etoposide plus durvalumab. In the JCOG 9702 study, which evaluated carboplatin and etoposide in ES-SCLC patients with a PS of 3 and aged less than 70 years or with a PS of 0–2 and aged 70 years or more, demonstrated that 63% of patients completed 4 cycles [8]. Our study will include only patients with a poor PS; therefore, if 50% of patients complete 4 cycles, the study treatment will be considered tolerable. If the expected percentage of completion in patients with a PS of 2 is 50%, the threshold percentage of completion is 33%, the one-sided alpha error is 0.1, and the beta error is 0.2, the required number of patients is calculated to be 41 based on the exact binomial distribution. If the expected percentage of completion in patients with a PS of 3 is 50%, the threshold percentage of completion is 20%, the one-sided alpha error is 0.1, and the beta error is 0.2, the required number of patients is calculated to be 12 based on the exact binomial distribution.

The total number of patients was calculated to be 56, considering the patients excluded from the analysis due to censoring. For the 1-year survival rate, which is the most important secondary endpoint, under the expected value of 26%, a threshold of 13%, and alpha error of 0.1 (one-sided), the power of the exact test for the binomial ratio is calculated to be 85 and 78% under all 53 patients (sum of those with a PS of 2 and 3) and 41 patients with a PS of 2, respectively.

This study was approved by the Niigata University Central Review Board of Clinical Research. All procedures will be performed in accordance with the ethical standards of the institutional and/or national research committee and with the 2013 Declaration of Helsinki and its later amendments or comparable ethical standards. All patients must provide written informed consent.

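### The tolerability criterion is worded as 50% completion, but the cohorts were sized with 50% as the expected rate; applied literally, power is 50% to 61%, not 80%

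*Protocol article*

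**What the plan says.** The Statistical analysis section says that tolerability, the primary endpoint, "will be evaluated based on the percentage of patients who complete four cycles of carboplatin and etoposide plus durvalumab". It cites 63% completion of four cycles in the earlier randomised phase 3 trial of carboplatin and etoposide. It notes that the present trial enrols only patients with a poor PS, and draws the criterion from that: "if 50% of patients complete 4 cycles, the study treatment will be considered tolerable". This is the only statement in the article of when the regimen counts as tolerable.

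The next sentences size the two cohorts, each with an expected completion rate of 50%. For PS 2, "the threshold percentage of completion is 33%, the one-sided alpha error is 0.1, and the beta error is 0.2", giving 41 patients. For PS 3, "the threshold percentage of completion is 20%, the one-sided alpha error is 0.1, and the beta error is 0.2", giving 12. Both sizes are attributed to the exact binomial distribution. The abstract gives an enrolment target of 43 with PS 2 and 13 with PS 3, 56 in total, to allow for exclusions from the analysis.

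**The concern.** The same 50% appears in two roles. In the criterion sentence it reads as a bar for the result. In the sample-size sentences it is the true rate at which the trial should succeed with 80% probability. One figure cannot serve both purposes. If the observed proportion must reach the true proportion, a trial succeeds only about half the time, whatever its size. A design with 80% power at 50% must therefore have its success cut-off below 50%.

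The primary conclusion is at stake. For a range of plausible results the exact test and the literal sentence give opposite answers, and the stated beta of 0.2 belongs only to the exact test.

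**Working it through.** **Inputs** (Statistical analysis section, except the enrolment target, which is in the abstract): expected rate p1 = 0.50 in both cohorts; rate to be excluded p0 = 0.33 (PS 2) and 0.20 (PS 3); one-sided alpha 0.1; beta 0.2; n = 41 and 12; enrolment 43 and 13. The analysed size may therefore be 41 to 43 in PS 2 and 12 to 13 in PS 3.

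**Formulas.** With X ~ Binomial(n, p), the exact test rejects at the smallest r for which P(X ≥ r | p0) ≤ 0.10. Its power is P(X ≥ r | p1). The literal criterion uses r = n/2, rounded up to a whole patient, and the same two tail probabilities give its type I error and power.

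**Step 1: reproduce the stated sizes.**
- PS 2: n = 41 is the smallest size with at least 80% power. Its cut-off is 18, with P(X ≥ 18 | 0.33) = 0.095 and P(X ≥ 18 | 0.50) = 0.826. At n = 40 the cut-off is also 18 and power is 0.785.
- PS 3: n = 12 is the smallest size. Its cut-off is 5, with P(X ≥ 5 | 0.20) = 0.073 and P(X ≥ 5 | 0.50) = 0.806. At n = 11 the cut-off is also 5 and power is 0.726.

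Both stated sizes reproduce, so the test behind them is known.

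**Step 2: compare the exact test with the literal 50% criterion.** Power is at a true 50%.

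| Cohort, n | Exact-test cut-off | Type I error | Power | 50% cut-off | Type I error | Power | Results where they disagree |
|---|---|---|---|---|---|---|---|
| PS 2, 41 | 18 (43.9%) | 0.095 | 82.6% | 21 | 0.012 | 50.0% | 18–20 |
| PS 2, 42 | 19 (45.2%) | 0.066 | 78.0% | 21 | 0.017 | 56.1% | 19–20 |
| PS 2, 43 | 19 (44.2%) | 0.083 | 82.0% | 22 | 0.010 | 50.0% | 19–21 |
| PS 3, 12 | 5 (41.7%) | 0.073 | 80.6% | 6 | 0.019 | 61.3% | 5 |
| PS 3, 13 | 5 (38.5%) | 0.099 | 86.7% | 7 | 0.007 | 50.0% | 5–6 |

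For odd n the power of the literal criterion is exactly 50%, by symmetry of the binomial at p = 0.5. For even n it is higher, because a result of exactly half counts as success.

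**Step 3: chance that the two criteria disagree at a true 50%.** This is the difference between the two powers:
- n = 41: 82.6% − 50.0% = 32.6%
- n = 42: 78.0% − 56.1% = 21.9%
- n = 43: 82.0% − 50.0% = 32.0%
- n = 12: 80.6% − 61.3% = 19.3%
- n = 13: 86.7% − 50.0% = 36.7%

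**Step 4: true rate needed for 80% power under the literal criterion.** It is about 57% at n = 41 and about 58% at n = 12, both above the planned 50%.

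**The case against.** The strongest reply is that the sentence gives the reason for the expected rate. It follows the 63% benchmark, lowers it to 50% for a frailer population, and leads straight into calculations that use 50% as the expected rate. It names no number of completers and no cohort, and does not say that the observed rate must be at least 50%. The threshold, alpha and n that follow determine the exact-test cut-off uniquely. This reading may well be the intended one. If so, the sample sizes are sound. What remains is that the sentence states a verdict on the treatment, and nothing in the article marks it as a planning assumption.

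A reader might go further and infer any of three things that the document does not support.
- *The trial is too small.* The sizes of 41 and 12 reproduce; the fault is in the stated criterion.
- *The sponsor is free to choose either answer once the data are in.* That assumes the full protocol and SAP, which are not shown, are also silent. An article may leave numerical cut-offs to them, so the absence of a cut-off here is not the complaint.
- *The 50% criterion makes a false claim of tolerability more likely.* It does the reverse, cutting type I error to about 1% to 2%. The cost is lost power.

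**Conclusion.** The point holds as an inconsistency between the worded criterion and the test that sized the trial. Applied literally per cohort, the criterion has power of 50.0% to 61.3% at the planned true rate (beta 0.39 to 0.50), against the stated 80%. It would reverse the exact-test conclusion for 18–20/41, 19–20/42, 19–21/43, 5/12 or 5–6/13.

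These figures assume that 50% means an observed rate of at least 50% and that it applies to each PS cohort separately, as the sizing does. The sentence itself does not say whether it applies per cohort or to all patients. If it applied to the pooled total, power at a true 50% would be 50.0% with 53 patients (27 needed) and 55.3% with 56 (28 needed). If the sentence was meant only to justify the expected rate, no power is lost and the error is confined to the wording. Under either reading the sentence needs correcting, because it bears on the primary conclusion.

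**What to change.** Before analysis, replace the criterion sentence with a rule of this kind: tolerability is concluded separately in each PS cohort if the exact one-sided binomial test at alpha 0.1 rejects a completion rate of 33% (PS 2) or 20% (PS 3). Give the cut-offs for the possible analysed sizes: at least 18/41, 19/42 or 19/43 in PS 2, and at least 5/12 or 5/13 in PS 3. Note that 19/42 has 78.0% power, slightly under the planned 80%. Describe 50% as the expected rate only.

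If the sponsor does want an observed 50% as the bar, keep it, say whether it applies per cohort, and restate the power as about 50% to 61%.

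The first option costs one sentence and no extra patients. The second also needs no extra patients, but the protocol would have to acknowledge power well below 80%.
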